# Point of care ultrasound-detected postoperative diaphragmatic dysfunction and its association with pulmonary complications after thoracic surgery: protocol for a prospective, observational study

**DOI:** 10.3389/fmed.2026.1759942

**Published:** 2026-03-02

**Keywords:** diaphragm, diaphragmatic dysfunction, diaphragmatic ultrasound, perioperative period, postoperative pulmonary complications, thoracic surgery, ultrasound application, ultrasound indicators

## Abstract

**Introduction:**

Postoperative pulmonary complications (PPCs) significantly impact recovery after thoracic surgery. Postoperative diaphragmatic dysfunction (PDD) may be a key risk factor but remains under-recognized, particularly regarding comparative data between video-assisted thoracoscopic surgery (VATS) and robot-assisted thoracic surgery (RATS). This study aims to investigate the association between PDD detected by point-of-care ultrasound (POCUS) and PPCs following minimally invasive thoracic surgery.

**Methods:**

This is a single-center, prospective observational study conducted at the Affiliated Cancer Hospital of Guangzhou Medical University. A total of 148 patients scheduled for elective pulmonary resection (VATS or RATS) will be enrolled. Diaphragmatic function will be assessed using POCUS at four time points: 1 day preoperatively (T0), 30 min post-extubation (T1), and on postoperative day 1 (T2) and 3 (T3). The primary measurements include diaphragmatic excursion (DE) and diaphragmatic thickening fraction (DTF). The primary endpoint is the incidence of PDD (defined as DE < 10 mm or negative) on postoperative day 1. Secondary endpoints include the incidence and severity of PPCs within 7 days postoperatively (defined by European Perioperative Clinical Outcome criteria), serial changes in DE and DTF, pain scores, and quality of recovery (QoR-15). Propensity score matching and multivariate regression will be used to adjust for confounders.

**Conclusion:**

This study will elucidate the relationship between POCUS-detected PDD and PPCs in patients undergoing VATS and RATS. The findings may support the integration of diaphragmatic ultrasound into perioperative risk stratification and guide targeted preventive strategies to improve postoperative outcomes.

**Trial registration:**

https://www.chictr.org.cn, ChiCTR2500103734.

## Introduction

1

Lung resection is an important treatment for treating benign and malignant lung diseases. However, postoperative pulmonary complications (PPCs) remain a major factor affecting patient recovery. It has been reported that the incidence of PPCs in thoracic surgery including thoracotomy and minimally invasive surgery is as high as 20–45% (1–5) and this incidence range is summarized based on studies with complete postoperative 7-day follow-up and PPCs defined in accordance with the European Perioperative Clinical Outcome (EPCO) criteria (6). PPCs not only prolong hospital stays but also increase medical costs and mortality rates (7, 8). In recent years, minimally invasive surgical methods, such as video-assisted thoracoscopic surgery (VATS) and robot-assisted thoracic surgery (RATS) have been widely adopted due to their advantages of less trauma and faster recovery. As compared to the standard thoracotomic approach, minimally invasive surgeries decrease surgical complications, postoperative pain, and the overall incidence of PPCs.

However, postoperative diaphragmatic dysfunction (PDD), as a potential risk factor for PPCs, has not been fully recognized in lung resection. The term diaphragmatic dysfunction includes eventration, weakness and diaphragmatic paralysis (9). The diaphragm is the primary inspiratory muscle, and its function directly affects postoperative respiratory mechanics and expectoration ability. Studies have shown that the incidence of PDD after thoracic surgery can be as high as 12.5–68%, and it is closely related to PPCs such as pulmonary infection and atelectasis (7, 10, 11). Traditional diagnosis includes radiography, fluoroscopy, pulmonary function tests, and stimulation of the phrenic nerve, with some limitations including exposure to ionizing radiation, intense patient cooperation and less sensitivity or specificity. However, point-of-care ultrasound (POCUS) offers a noninvasive and dynamic approach to assess perioperative diaphragmatic function. Ultrasound has shown to be useful for the detection of diaphragmatic dysfunction, with a high sensitivity (93%) and specificity (100%) for diaphragmatic neuromuscular disease, and it has been suggested as the technique of choice for assessing diaphragmatic movement on suspicion of malfunctioning (9). Spadaro et al. first introduced POCUS in thoracic surgery. They defined DD as diaphragmatic excursion (DE) < 1 cm and demonstrated an increased risk of PPCs in patients with early PDD (OR = 5.5) (7). Recent evidence further highlights a lower postoperative diaphragmatic excursion difference (DED) after video-assisted thoracoscopic surgery (VATS) can serve as an additional marker, which helps predict the risk of PPCs (11). Additionally, Daniel et al. reported that PDD predominantly occurs on the surgical side, persists until postoperative 3rd day, and independently prolongs hospital stays (OR = 1.3) (12). Diaphragmatic thickness (DT) and thickening fraction (DTF) are also critical metrics; DT reduction >10% or DTF <20% are defined as thresholds for clinically relevant atrophy in critically ill patients according to an expert consensus in 2022 (13), with the point that preoperative diaphragmatic atrophy (DT < 0.2 cm) significantly increases PPCs risk.

Some studies suggest that the outcomes of RATS are similar to or even better than those of VATS surgery (5, 14). Geraci et al. reported that the incidence of early postoperative complications in 253 patients who underwent RATS lung resection was only 6.4% (15). However, this study lacked long-term follow-up and the definition of PPCs may differ from that in many previous studies, which may have resulted in an underestimation of the incidence of PPCs. RATS, with its three-dimensional high-definition vision, flexible instruments and tremor filtering function, theoretically can reduce the intraoperative traction of the phrenic nerve and chest wall trauma (16); however, RATS-specific intraoperative factors such as CO2 insufflation (capnothorax) induce an artificial increase in intrathoracic pressure, which exerts direct mechanical and physiological effects on the diaphragm: the elevated intrathoracic pressure antagonizes the abdominal-to-thoracic pressure gradient generated by diaphragmatic contraction, directly reducing the effective excursion amplitude of the diaphragm; sustained intrathoracic hypertension compresses the intrathoracic microvasculature, impairs local microcirculatory perfusion of the diaphragmatic muscle fibers, and hinders oxygen supply and metabolite excretion of the muscle tissue; in addition, the diaphragm needs to maintain a higher contractile tension to overcome the increased intrathoracic pressure during the surgical period, which easily induces early fatigue of the diaphragmatic muscle fibers. These changes may alter diaphragmatic excursion and contractility in the perioperative period, in contrast to VATS, which does not require artificial CO2 insufflation to establish a pneumothorax and maintains intrathoracic pressure at a physiological level without the above-mentioned diaphragm function interference factors—an aspect rarely addressed in previous studies. Patients can be discharged on the first day after RATS lung resection, and both the clinical effect and patient satisfaction are excellent (15). Early research by Mahieu et al. showed that the proportion of emergency conversion to thoracotomy during RATS was significantly lower than that of traditional video-assisted thoracoscopic surgery (VATS) (3.6% vs. 14.3%), suggesting its potential safety advantage (17). Despite these advances, current studies predominantly focus on single-timepoint assessments of diaphragmatic function or single minimally invasive surgical modality, lacking longitudinal data comparing VATS and RATS across the perioperative period.

Based on these, we conducted a prospective cohort design, combined with perioperative multi-time point POCUS monitoring of diaphragm function, to explore the correlation between PDD and PPCs after minimally invasive thoracic surgery (VATS and RATS). Additionally, the risk factors for PPCs will be screened out, by integrating perioperative diaphragm ultrasound monitoring with ARISCAT, we also aim to verify whether this predictive efficacy will be improved.

## Methods and analysis

2

### Study design

2.1

This was a non-randomized, single-center, prospective observational study conducted at the Affiliated Cancer Hospital of Guangzhou Medical University. One hundred and forty-eight patients who underwent elective pulmonary resection for lung disease between July 2025 and May 2026 were included. Figure 1 is the study timeline. Bilateral diaphragm function was monitored by ultrasound at 4 time periods, 1st day before surgery (T0), 30 min post-extubation in the Post-anesthesia Care Unit (PACU) (T1), 1st day after surgery (T2), and 3rd day after surgery (T3). This standardized T1 measurement window will be uniformly applied to all enrolled patients in the study. Diaphragm thickness at the end of inhalation (DTei), diaphragm thickness at the end of exhalation (DTee), and DE during voluntary calming respiration were recorded at each time period. The occurrence of patients’ PPCs was tracked and observed during the 7 day postoperative period, and related clinical variables were recorded, respectively. Figure 2 is the trial flow chart.

**Figure 1 fig1:**
[figure not shown]
Timeline of the research process.

**Figure 2 fig2:**
[figure not shown]
Flow chart of the study.

### Inclusion and exclusion criteria

2.2

Inclusion criteria:

(1) Age between 18 and 80 years.(2) American Society of Anesthesiologists (ASA) Physical Status I–III.(3) BMI between 18.5 and 30 kg/m^2^.(4) Scheduled to undertake RATS/VATS lobectomy/segmentectomy.(5) Signed the informed consent form.

Exclusion criteria:

(1) Those with neuromuscular disorders (e.g. Guillain-Barré syndrome, myasthenia gravis).(2) Those with a history of upper abdominal/thoracic surgeries.(3) Those with preoperative severe pulmonary complications (such as pulmonary infection, pleural effusion, atelectasis, respiratory failure, or cardiopulmonary edema).(4) Those of which we cannot obtain a satisfactory ultrasound imaging or do not have space for placement of the ultrasonic probe.(5) Those with diaphragm insufficiency preoperatively (determined by a combination of preoperative pulmonary function tests, point-of-care ultrasound (POCUS) assessment, and clinical manifestations such as persistent dyspnea or decreased exercise tolerance, without relying on phrenic nerve stimulation).(6) When minimally invasive surgical approaches convert to thoracotomy in operation.(7) Those with severe cardiac diseases, or hepatic and renal dysfunction (in such patients, drug metabolism is significantly impaired, and residual muscle relaxants and anesthetics may persist after intubation, thereby inhibiting diaphragmatic movement).(8) Withdrawal from the study or withdrawal of informed consent during the study.(9) Immediately transferred to the ICU ward after surgery due to major adverse events such as intraoperative massive hemorrhage and refractory hypoxemia requiring mechanical ventilation (such patients will be transferred to the ICU with endotracheal intubation for continued respiratory support, resulting in significantly prolonged mechanical ventilation time, which will further impair diaphragmatic function).

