Severe	Significantly prolonged hospitalization, resulting in permanent functional limitations or death	Requires aggressive treatment (e.g., mechanical ventilation, ICU admission)

Mild: transient postoperative hypoxemia requiring short-term oxygenation.

Moderate: pneumonia requiring intravenous antibiotic therapy that has not progressed to respiratory failure.

Severe: acute respiratory distress syndrome (ARDS) requiring tracheal intubation and ICU monitoring.

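### Exclusion criteria 6 and 9 remove enrolled patients for events during or just after surgery, which can bias PPC incidence and severity and the VATS–RATS comparison

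*Protocol article*

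**What the plan says.** Entry is defined before the operation. Section 2.2 admits patients "Scheduled to undertake RATS/VATS lobectomy/segmentectomy" who have consented, and Section 2.1 begins measurement at "1st day before surgery (T0), 30 min post-extubation in the Post-anesthesia Care Unit (PACU) (T1"). The exclusion list in Section 2.2 also holds two events that cannot be known at that time:

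- Criterion 6: "When minimally invasive surgical approaches convert to thoracotomy in operation". No reason is given.
- Criterion 9: "Immediately transferred to the ICU ward after surgery due to major adverse events such as intraoperative massive hemorrhage and refractory hypoxemia requiring mechanical ventilation". The reason given is that prolonged ventilation would further impair the diaphragm.

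Section 2.4.7 lists respiratory failure among the PPCs. Table 2 describes the management of a severe PPC as "Requires aggressive treatment (e.g., mechanical ventilation, ICU admission"), and the worked example beneath it is "Severe: acute respiratory distress syndrome (ARDS) requiring tracheal intubation and ICU monitoring". Incidence and severity of PPCs form a secondary endpoint (Section 2.7.2), and surgical technique is named as a candidate risk factor for PPCs (Section 2.6.2).

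On conversion, the Introduction cites one study in which the "proportion of emergency conversion to thoracotomy during RATS was significantly lower than that of traditional video-assisted thoracoscopic surgery (VATS) (3.6% vs. 14.3" (both figures are percentages). Section 2.9 plans 1:1 propensity matching of VATS and RATS on baseline characteristics. It also rejects listwise deletion because of selection bias. The limitations in the Discussion attribute selection bias to the lack of randomisation and do not mention these two exclusions.

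**The concern.** Both criteria select patients on consequences of the operation, although they are listed as eligibility traits. Two problems follow.

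First, criterion 9 overlaps an outcome. A patient who goes straight to the ICU ventilated for refractory hypoxaemia resembles the severe end of the PPC scale, yet is dropped from the cohort in which that scale is reported.

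Second, criterion 6 may act unequally. If conversion is more frequent with one approach and converted patients fare worse, removing them flatters that approach. Matching on age, BMI, ASA class and tumour complexity balances what was known before surgery and cannot undo selection on a later event. Multiple imputation fills gaps in retained patients and does not bring back patients who were removed.

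At stake are the PPC incidence and severity figures and the VATS–RATS comparison. The PDD–PPC association is less exposed.

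**Working it through.** **Inputs from the protocol.** N = 148, PPC incidence 37%, PDD incidence 30%, odds ratio 3.0, alpha 0.05, power 0.80, dropout 10% (Section 2.8). Conversion 14.3% VATS and 3.6% RATS (Introduction, one cited study).

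**Assumptions.** A two-sided test. A 74:74 split, since the protocol gives none (range 98:50 to 50:98). PPC risk in converted patients, also not given, so shown as a range.

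**1. The plan's own sample size.** n = (1.960 + 0.842)² / [0.37 × 0.63 × 0.30 × 0.70 × (ln 3)²] = 132.8, so 133. Then 133 / 0.90 = 147.8, so 148. The stated figure reproduces and is not in dispute.

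**2. Patients removed by criterion 6.**

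| Split VATS:RATS | VATS removed | RATS removed | Total | Share of 148 |
|---|---|---|---|---|
| 74:74 | 74 × 0.143 = 10.6 | 74 × 0.036 = 2.7 | 13.2 | 9.0% |
| 98:50 | 14.0 | 1.8 | 15.8 | 10.7% |
| 50:98 | 7.2 | 3.5 | 10.7 | 7.2% |

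**3. Bias in PPC incidence.** If converted patients exceed the others in risk by a gap g, and a fraction c converts, dropping them understates incidence by c × g.

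| g (assumed) | VATS | RATS | Bias in the difference, favouring VATS |
|---|---|---|---|
| 0 points | 0 | 0 | 0 |
| 20 points | 0.143 × 20 = 2.9 | 0.036 × 20 = 0.7 | 2.1 points |
| 30 points | 0.143 × 30 = 4.3 | 0.036 × 30 = 1.1 | 3.2 points |

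At 74:74 the pooled incidence is understated by 0.0895 × 20 = 1.8 to 0.0895 × 30 = 2.7 points.

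**4. The same effect as an odds ratio.** Let the true PPC risk be p = 37% in both groups and q the risk in converted patients. The observed rate is (p − c × q) / (1 − c).

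| q (assumed) | RATS observed | VATS observed | Spurious OR, RATS vs VATS |
|---|---|---|---|
| 37% | 37.0% | 37.0% | 1.00 |
| 50% | 36.5% | 34.8% | 1.08 |
| 60% | 36.1% | 33.2% | 1.14 |
| 80% | 35.4% | 29.8% | 1.29 |

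**5. Primary endpoint.** With true PDD at 30% and, as an assumption, PDD in half of converted patients, the same formula gives a pooled observed PDD of 28.0%. The protocol has no PDD rate for converted patients, so this is illustration only.

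**6. Power.** The 13.2 removals compare with a dropout allowance of 148 × 0.10 = 14.8. If they come on top of a 10% dropout and nobody is replaced, (148 − 13.2) × 0.90 ≈ 121 remain. Power by the formula in step 1 then falls from 0.80 to about 0.76. The text does not say whether excluded patients are replaced.

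**The case against.** The strongest defence is that the restriction suits the main question. The primary objective concerns minimally invasive surgery, the sample size is set for the PDD–PPC association, and a converted patient has had a thoracotomy. DE is defined in quiet voluntary breathing and T1 falls 30 minutes after extubation, so a ventilated patient cannot supply those readings. Where respiratory failure precedes the day 1 scan, PDD on that scan cannot have predicted it. All of this stands, and it makes the completed minimally invasive cohort a defensible population for the association. It does not justify discarding known PPC outcomes from the incidence, severity and VATS–RATS analyses.

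It is also fair that the bias is modest. At 37% incidence and 74 per group, the 95% interval for a difference has a half-width of 1.96 × √(2 × 0.37 × 0.63 / 74), about 16 points, against a bias of 2 to 3 points. No VATS–RATS hypothesis is powered. But the bias is systematic, and the plan has no step that would reveal it.

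A reader might infer more than the documents support:

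- **That both exclusions are known to fall unequally.** A difference is cited for conversion only, from one study of emergency conversion that is not this centre's experience. The surgeons here had already done more than 50 RATS cases. There is no by-approach figure for ICU transfer.
- **That the severe grade is emptied.** Only immediate transfers are lost, and some of those follow haemorrhage. PPCs are recorded on days 1 to 7, so later reintubation or ICU admission in retained patients still counts.
- **That PDD incidence is shown to be understated.** The Introduction says only that PPCs are fewer with minimally invasive surgery than with thoracotomy. Neither a PDD nor a PPC rate is given for converted patients.
- **That the dropout allowance is exceeded.** At 74:74 the conversions alone stay within it.

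**Conclusion.** The point holds in a limited form. Criteria 6 and 9 remove enrolled patients on events caused or affected by the operation, and neither matching, covariate adjustment nor multiple imputation corrects for this. Criterion 9 removes some early cases that match the severe PPC grade; how many cannot be estimated from the documents. Criterion 6 may remove about 10.6 VATS and 2.7 RATS patients (9.0% of 148). That rests on the cited conversion rates applying here and on an even split.

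The resulting bias in the VATS–RATS PPC comparison is 2.1 to 3.2 points in favour of VATS, with pooled incidence understated by 1.8 to 2.7 points, if converted patients carry a PPC risk 20 to 30 points higher. The size of that gap is assumed, and its direction is inferred from the Introduction's contrast with thoracotomy. With no gap the bias is zero. Any effect on PDD incidence is inference, and the PDD–PPC association in completed minimally invasive surgery remains a legitimate analysis.

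**What to change.** - For PPC incidence and severity, and for VATS versus RATS, keep every consenting patient whose surgery starts. Analyse by planned approach and count PPCs in converted and ICU-transferred patients.
- Report the numbers of conversions and immediate ICU transfers by planned approach.
- Keep the completed minimally invasive cohort for the PDD–PPC association, or as a sensitivity analysis, and label it as such.
- Where DE on day 1 cannot be measured, treat PDD as missing. Add best-case and worst-case bounds to the planned multiple imputation, because values absent in ventilated patients may be missing not at random.
- Keep criterion 8 but restate it as a withdrawal rule that respects consent. It should not be deleted with the others.
- Name the two post-enrolment exclusions in the limitations wherever the restricted cohort is reported.

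The cost is revised wording, plus chart follow-up of roughly a dozen converted patients (at the cited rates) and any ICU transfers. The downside is a more heterogeneous cohort with some missing day 1 scans.

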### Diaphragmatic ultrasound protocol

2.3

#### Operating process

2.3.1

1st day before surgery (T0), 30 min post-extubation in the Post-anesthesia Care Unit (PACU) (T1), 1st day after surgery (T2), and 3rd day after surgery (T3), diaphragmatic ultrasound was performed with the patient in a semi-recumbent position in bed with the head of the bed elevated by 30° performing quiet breathing. We recorded DE during voluntary calming respiration (7) (excluding deep inspiration and sniff manoeuver, as these two maneuvers are associated with poor compliance in postoperative patients due to pain and chest drain tube interference), we evaluated both left and right hemidiaphragms. To standardize the acoustic window across time points, preoperatively (T0) we mark the probe position on the chest wall using skin-friendly, non-irritating markers, recording the distance from the midclavicular line/anterior axillary line and rib interspace. Postoperatively, if surgical dressings, chest tubes, or subcutaneous emphysema block the original site, we adjust the probe to the nearest adjacent interspace while maintaining the same anatomical orientation relative to the diaphragm dome, documenting the adjustment in the case report form. All diaphragmatic ultrasound measurements at T0–T3 time points are performed by the same fixed team consisting of 1 experienced independent anesthesiologist and 1 resident trainee, both of whom have completed 3 months of specialized training in diaphragmatic ultrasound, to minimize inter-observer variability. The independent anesthesiologist always performed the measurements by first marking the best acoustic window on the patient’s chest for the trainee’s observation of the measurements.

DE was assessed using a 3.5–5 Mhz convex ultrasound probe with the liver and spleen as the ultrasound windows for the right and left hemidiaphragm, respectively. To show the right hemidiaphragm, the probe was placed between the midclavicular and anterior axillary line intercostals, whereas for the left hemidiaphragm, a subcostal or low intercostal probe position was chosen between the anterior midaxillary line. For left hemidiaphragm measurement, if the splenic acoustic window is insufficient (unclear diaphragm visualization for ≥3 consecutive breathing cycles), we adjust the probe angle, increase the imaging depth (up to 6 cm), or use the left subcostal approach with the patient slightly rotated to the right. If visualization remains unsuccessful, we document the left hemidiaphragm as “unmeasurable” and focus on the right hemidiaphragm (especially the surgical side, if unilateral resection) for analysis. The hemidiaphragm probe line was selected using the two-dimensional mode (B mode). The probe was fixed to the chest wall with the ultrasound probe located medially, cephalad, and dorsally so that the ultrasound beam reached the posterior portion of the hemidiaphragm dome at an angle as close to 90 as possible, and then the ultrasonography machine was switched to the motion mode (M mode). Using anatomical M-mode (AMM), during inspiration, the normal diaphragm contracted and moved caudally toward the transducer; this was recorded as an upward movement tracked by the motion mode and was regarded as a diaphragmatic excursion during inspiration, which was measured on the vertical axis from baseline to maximum inspiratory height on the frozen image, and the resultant was the DE (Figure 3) (18, 19). Similarly, the left hemi-transverse diaphragm mobility was measured under the splenic window.

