#### Diagnosis to PDD

2.3.2

DE values less than 10 mm or negative (7) [based on our preliminary experiments and others’ studies, the strong association between this critical value and diaphragmatic function has been validated (23)] is our primary measurement. Diaphragmatic weakness is determined where there is decreased DE with or without paradoxical movement during the sniff manoeuver. DTF values below 20% were interpreted as indicative of diaphragm paralysis (9, 13, 24).

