#### Primary endpoint

2.7.1

Incidence of PDD (DE values less than 10 mm or negative) at 1 day postoperatively.

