
For missing data including unmeasurable left hemidiaphragm ultrasound measurements, Multiple Imputation (MI) will be used to handle incomplete observations at any time point (T0–T3), with 20 imputed datasets generated. Listwise deletion will not be adopted to avoid selection bias and preserve statistical power. All statistical analyses were performed using SPSS software Version 26.0 (IBM, United States) and R software (Version 4.3.0) with packages “lme4” (for LMM) and “mice” (for MI).

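### The primary endpoint does not say which hemidiaphragm counts, and the plan gives two conflicting rules for a left side that cannot be measured

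*Protocol article*

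**What the plan says.** - **Sides scanned.** Section 2.3.1 of the protocol article states "we evaluated both left and right hemidiaphragms", and section 2.1 has bilateral monitoring at T0 to T3. Each patient can therefore have two excursion (DE) values at T2.
- **Definition and endpoint.** Section 2.3.2 gives "DE values less than 10 mm or negative" as the primary measurement. Section 2.7.1 gives "Incidence of PDD (DE values less than 10 mm or negative) at 1 day postoperatively". Neither names the operated, right, either, worse or both sides.
- **Unmeasurable left side, section 2.3.1.** If adjusting the probe fails, the left side is documented as unmeasurable and the team is to "focus on the right hemidiaphragm (especially the surgical side, if unilateral resection) for analysis".
- **Unmeasurable left side, section 2.9.** "For missing data including unmeasurable left hemidiaphragm ultrasound measurements, Multiple Imputation (MI) will be used", at any of T0 to T3, with 20 imputed datasets and no listwise deletion.
- **Where PDD is expected.** The Introduction cites a study reporting that "PDD predominantly occurs on the surgical side".
- **Exclusion (4), section 2.2.** "Those of which we cannot obtain a satisfactory ultrasound imaging or do not have space for placement of the ultrasonic probe". No side or time point is given.

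**The concern.** Two DE values per patient and a threshold without a side do not define one binary endpoint. The same variable is the exposure in the regression of pulmonary complications (PPCs) on PDD that sized the study (2.8), and its threshold is what the ROC analysis in 2.9 sets out to validate. The choice of side therefore carries through to the main results.

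The two rules for an unseen left side cannot both fix the same patient's PDD status at the same visit: one takes it from the right side, the other from an imputed left value. The 2.3.1 rule also works against itself. After a left resection the right side is not the surgical side, yet the parenthesis gives priority to the surgical side. Followed literally, it replaces the side where PDD is expected with the side where it is less expected. Under an operated-side reading of the endpoint, this happens in left-sided resections only. Unless one rule is fixed beforehand, it could be chosen after the results are known.

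**Working it through.** **1. The plan's own figure.** Inputs from 2.8: PDD 30%, PPC 37%, OR 3.0, alpha 0.05 (taken as two-sided), power 0.80, dropout 10%.

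N = (1.960 + 0.842)² / [0.37 × 0.63 × 0.30 × 0.70 × (ln 3)²] = 7.849 / 0.0591 = 132.8, so 133 evaluable. 133 / 0.90 = 147.8, so 148.

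The stated 148 reproduces, so the sample-size arithmetic is not at fault. The 30% in it is also given without a side.

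**2. The two rules applied to one patient at T2, left side unmeasurable, operated-side endpoint.**

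| Operation | Section 2.3.1 | Section 2.9 |
|---|---|---|
| Right resection | PDD from the right (operated) side | Same; the imputed left value does not matter |
| Left resection | PDD from the right (non-operated) side | PDD from the imputed left (operated) side |

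The rules agree after a right resection and conflict after a left one.

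**3. Size of the substitution.** The documents give no share of left-sided operations, no rate of unmeasurable left sides and no PDD rate on the non-operated side. Assumptions: left-sided share 0.5; operated-side PDD 0.30 (the figure in 2.8, read as operated-side); other side 0.05; left unmeasurable in a share u, unrelated to PDD.

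Incidence when the right side is read = 0.30 − 0.5 × u × (0.30 − 0.05)

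| u | Overall incidence | Incidence in left resections (0.30 − 0.25u) | Cases lost of 148 (148 × 0.125u) |
|---|---|---|---|
| 0.10 | 28.75% | 27.5% | 1.9 |
| 0.20 | 27.5% | 25.0% | 3.7 |
| 0.30 | 26.25% | 22.5% | 5.6 |

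With every operated side read, 148 × 0.30 = 44.4 cases are expected.

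**4. Size of the open side definition.** With every side measurable, sides independent, other-side PDD 5 to 10% and left-sided share 40 to 50% (all assumed):

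- operated side: 30%
- either side: 1 − 0.70 × 0.95 = 33.5%, up to 1 − 0.70 × 0.90 = 37%
- always the right side: 0.5 × 0.30 + 0.5 × 0.05 = 17.5%, up to 0.6 × 0.30 + 0.4 × 0.10 = 22%
- both sides: 0.30 × 0.05 = 1.5%, up to 0.30 × 0.10 = 3%

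Under these assumptions the side definition moves the incidence more than the handling of an unseen left side does.

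**The case against.** **The two rules can be reconciled.** Focusing on the right side need not mean substituting it. Section 2.3.1 could describe which measured data are used, and 2.9 how the dataset is completed. That is possible, and substitution is partly an inference. But no section assigns the rules to different analyses, and 2.3.1 says its rule is for analysis. The conflict stays open in the text.

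**A fuller document may name the side.** It may, and an article condenses. That would not remove the conflict between two rules that this document does state.

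**The effect is small and assumed.** This stands. The shift of 1.25 to 3.75 points is less than the 95% half-width for 30% in 133 patients: 1.96 × √(0.30 × 0.70 / 133) = 7.8 points. However, it is a systematic shift, confined to one operated side, and can be avoided without cost.

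**Stronger readings that the documents do not support.**

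- A reader might count exclusion (4) as a third contradictory rule and work out lost patients and power. The criterion names neither side nor time point and reads most naturally as a screening or no-image criterion. Later use is conceivable, since items (6), (8) and (9) of the same list are events after enrolment, but it is not stated. A loss of sample size does not follow.
- A reader might infer that emphysema, dressings or drains remove patients. Section 2.3.1 deals with these by moving the probe to the nearest adjacent interspace and documenting the change.
- A reader might infer that patients with low DE at T0 are counted as postoperative cases. Exclusion (5) includes preoperative ultrasound, and whether it lets such patients through depends on how its combination of criteria is read. That is a separate question.

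**Conclusion.** The point holds in two parts. First, the PDD definition and the primary endpoint name no side although two are measured, so the endpoint cannot be computed uniquely. Second, sections 2.3.1 and 2.9 give different rules for an unmeasurable left side, and following 2.3.1 after a left resection can record true PDD as absent.

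Neither part depends on the assumed figures. The size does: incidence falls from 30% to about 28.8 to 26.3%, given half of resections left-sided, 30% and 5% PDD on operated and other sides, and 10 to 30% of left sides unmeasurable independently of PDD. Misclassification of this kind would be expected to weaken the PDD–PPC association, but by how much has not been calculated. Because the primary endpoint is affected, the sections should be reconciled before the T2 data are analysed.

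**What to change.** - **2.3.2 and 2.7.1:** state one side rule. DE on the operated side at T2 follows the protocol's own rationale; either-side PDD can be a secondary or sensitivity analysis. Another rule would also be workable, provided it is stated once and used throughout.
- **2.3.1:** delete the instruction to use the right side in place of an unmeasurable left. Treat an unmeasurable operated side as missing, to be handled by the multiple imputation already in 2.9. Under an operated-side rule, an unmeasurable non-operated side does not affect the primary endpoint.
- **2.2, exclusion (4):** state that it applies at screening, so that it cannot be set against the rejection of listwise deletion in 2.9.
- **Optional:** a sensitivity analysis using the T0 DE already collected. A T0 threshold in the endpoint itself is not needed to resolve this point.

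The cost is wording in these sections. Section 2.10 already records surgical side, DE at each visit and the measurability of each hemidiaphragm, so no new data are needed.
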